**Methods:**

A total of 54 men and women aged 60 years or older with no history of diabetes and warfarin and vitamin K use will be recruited. Screening tests will be performed, including those for functional, anthropometric, and clinical presentation. On the basis of muscle quality, a combined equation of lean mass (leg appendicular skeletal muscle mass in kg) and strength (leg press; one-repetition maximum), participants will be stratified into a high or low muscle function group and randomized into the controlled crossover acute intervention. Three visits will be performed approximately 7 days apart, and acute aerobic exercise, acute resistance exercise, and a control session (rest) will be completed in any order. Our primary outcome for this study is the effect of acute exercise on ucOC in older adults with low muscle function and those with high muscle function.

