### Hypotheses

We hypothesize that older adults with lower muscle function, compared to those with normal or higher muscle function, will (1) be characterized by lower levels of circulating ucOC and those with lower ucOC will be associated with poorer glucose control and (2) be characterized by abnormal skeletal muscle signaling (muscle hypertrophic or atrophic pathways). Both AER and RE will increase ucOC; however, we hypothesize that this will be to a greater degree in those with lower muscle function. We will test these hypotheses at baseline and after acute exercise. This project has the potential to identify novel biomarkers for interactions between bone and muscle, with implications for future drug targets or clinical interventions and the management of those with or at risk of sarcopenia or reduced muscle function.

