**Description of interventions**
Aerobic exercise: Performed on the cycle ergometer for 30 minutes at an intensity corresponding to 70%-75% of peak heart rate; this is based on data obtained from the exercise capacity assessment. Intensity will be adjusted every 5 minutes to maintain the desired heart rate range.Resistance exercise: The protocol is as we have previously performed [10] and includes 30 minutes of strength and power exercises at intensities corresponding to 70%-75% of the predetermined one-maximal repetition based on the individual’s test results. Leg press will be performed as 5 sets of 10 rapidly concentric (as fast as possible) and slow eccentric (4 seconds) repetitions. Recovery between sets and exercise will be 2 minutes. Participants will also perform jumping sequences as 5 sets of 10 jumps (jumping as high as they can 10 times without stopping). Power training is effective to increase muscle strength and bone density and is safe for older adults [73-75].Control: This session will include 30 minutes of supine bed rest.

All testing visits will be monitored and supervised by accredited exercise physiologists (AEPs), who will follow the structured protocol as dictated for that particular session (AER, RE, and CON). The AEP will also monitor signs and symptoms in response to exercise training and will record Borg RPE, blood pressure, and heart rate at frequent time points. Any adverse signs and symptoms will be documented, including feelings of fatigue, soreness, light-headedness, and any injuries. Blood sampling and intravenous cannulation will be performed by personnel who are experienced in the technique, and muscle biopsy will be performed by an experienced medical physician.

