##### Control Procedures

For testing visits 3, 4, and 5, participants will arrive at the laboratory between 7 AM and 8 AM following an overnight fast and with abstinence from exercise or reduced general activity (ie, heavy to moderate activities of daily living) in the preceding 24 hours and for all follow-up sessions. These sampling procedures will be followed at all visits to account for circadian or diurnal rhythms [76]. Participants may be requested to abstain from particular medications (eg, aspirin), as advised by the medical doctor, if electing for a muscle biopsy.

To assist with adherence to study protocols, participants will be monitored via regular communication with the study coordinator on the days preceding each study visit. As a general consideration for participation in this study, participants will be encouraged not to alter their current physical activity levels, exercise habits, or dietary intakes for the entirety of the study. Participants are asked to report whether there have been any alterations in medications throughout the study, as we request that all medication interventions are stable for at least more than three months.

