#### Statistical Analysis and Determination of Sample Size

The primary endpoint for this study is the change in ucOC levels from baseline to the peak, postintervention sampling time point. The analysis will include a comparison of changes in ucOC levels in response to each intervention from baseline to postintervention sampling time points (0, 30, 60, and 120 minutes) between the low muscle function and normal or high muscle function groups, by using repeated measures analysis of variance (ANOVA). Comparisons of multiple means will be examined using a 2-factor (exercise type×time point) repeated measures ANOVA. For all significant interaction and main effects, a priori comparisons of means (baseline vs all postexercise time points) will be conducted using the Fisher least significant difference test (*P<*.05). Multivariable regression models will be used to determine associations between selected measurements, adjusting for BMI and sex. Data will be analyzed using the Statistical Package for the Social Sciences, version 22 (SPSS Inc), and statistical significance will be declared at *P*<.05.

In 10 postmenopausal women, we previously reported that the change in ucOC levels following exercise is approximately 9% [39]. We will recruit 54 participants (equal number of men and women) who will be dichotomized as low muscle function versus high muscle function (27 per group). After adjusting for a loss to follow-up rate of 10% (5.4/54), this sample size will be large enough to detect an estimated 4% difference in changes in ucOC levels (SD 6%) between groups with a type I error rate of 5%, type II error rate of 20%, and power of >80% (G*Power 3.1.9.2 for Windows) [92].

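### The only named follow-up comparisons set post-exercise ucOC against baseline; no AER-versus-rest or RE-versus-rest contrast is named to support a claim that either exercise raises ucOC

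*Protocol article*

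**What the plan says.** The Hypotheses section makes a directional claim about exercise itself: "Both AER and RE will increase ucOC; however, we hypothesize that this will be to a greater degree in those with lower muscle function". The first half of that sentence is the subject here. The second half is the group question.

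The design supplies a comparator, described in the intervention textbox: "Control: This session will include 30 minutes of supine bed rest". The primary outcome section lists AER, RE and CON as the three interventions, with blood samples at 0, 30, 60 and 120 minutes after each.

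The section Statistical Analysis and Determination of Sample Size sets out three steps:

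- The group comparison is made "between the low muscle function and normal or high muscle function groups, by using repeated measures analysis of variance (ANOVA").
- Conditions are then examined together: "Comparisons of multiple means will be examined using a 2-factor (exercise type×time point) repeated measures ANOVA".
- The follow-up is triggered by a broad condition, "For all significant interaction and main effects", and consists of one set of tests: "a priori comparisons of means (baseline vs all postexercise time points) will be conducted using the Fisher least significant difference test".

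Two other passages bear on what those tests measure. Control Procedures standardises arrival time and fasting: "These sampling procedures will be followed at all visits to account for circadian or diurnal rhythms". Biospecimen Sampling Protocols states that the resting sample is drawn at the first visit only and serves as baseline for the later visits.

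**The concern.** To say that AER or RE raises ucOC, post-exercise ucOC has to be compared with post-rest ucOC at the same point of the session. The named follow-up asks instead whether post-exercise ucOC differs from one resting sample. The two questions have different answers whenever ucOC moves for reasons other than exercise, and the design allows two such reasons:

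- **Change over the session.** Each visit lasts about three hours, in the morning and fasted. A fixed arrival time makes the diurnal component similar across visits but leaves it inside each baseline-to-post difference.
- **Change between visits.** With one baseline at the first of the three acute visits and a randomised order, each condition falls on a later visit for about two-thirds of participants. For them the comparison spans different days.

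An upward drift can look like an exercise response, and a downward drift can hide one. The rest session can separate these, but the only pairwise tests named make no use of it as a comparator.

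**Working it through.** **Plan's own figure.** There is none for this comparison. The stated power of more than 80% concerns the low-versus-high group contrast, so only its SD and loss rate are borrowed here.

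**Inputs from the statistical section.** 54 recruited with 10% loss: 54 × 0.9 = 48.6, taken as 48 completers. SD of change 6%, stated for changes compared between groups and assumed to apply to a baseline-to-post change. Test level .05. Planning response about 9%.

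**Assumptions not in the documents.** No exercise effect. A drift of 0 to 3%, identical in AER, RE and CON. Between-day variance at 25%, 50% or 75% of the within-person variance.

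**Step 1: one baseline-versus-post test, no gate.** The standard error is 6/√48 = 0.866. The standardised shift is drift/0.866: 1.15 for 1%, 2.31 for 2% and 3.46 for 3%. Two-sided rejection at .05 is about 20%, 62% and 92%. A 2% drift is less than a quarter of the planning response (2/9 = 22%).

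**Step 2: the rule as written, simulated.** Within-person variance is 6²/2 = 18 per sample, so a between-day change has SD 6%. There is one shared baseline and four post samples in each of three conditions. The gate is any of the three omnibus tests (type, time, interaction) at P<.05. Paired baseline-versus-post tests at P<.05 follow, counting rises in AER or RE. Step drift is complete by the 0-minute sample; linear drift reaches the stated size at 120 minutes. Ranges cover the three variance splits.

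| Common drift | Any AER or RE rise, step | Any rise, linear | AER at 60 min, step | AER at 60 min, linear |
|---|---|---|---|---|
| 0 | about 4% | about 4% | about 1% | about 1% |
| 1% | 36-44% | 24-29% | 17-24% | 8-11% |
| 2% | 88-94% | 80-90% | 65-74% | 28-35% |
| 3% | over 99% | about 99% | 94-98% | 57-66% |

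**Step 3: contrasts with rest.** AER minus CON and RE minus CON, on the mean of the four post samples, each two-sided at 2.5%, declare a rise in about 2-3% of the same trials at every drift. A check using the highest post sample in place of the mean also gave about 2-3%.

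**Step 4: the omnibus interaction.** With CON as a level and a sphericity correction, the exercise type by time interaction rejects in about 3-5% of trials at every drift, so common drift does not inflate it. The time main effect does respond to drift, and it alone opens the follow-up.

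**Step 5: what the contrast costs in precision.** With the variance split equally (9 between days, 9 residual), the SD of exercise minus CON on four-sample means is √[2(9 + 9/4)] = √22.5 = 4.7%. A single baseline-versus-post difference has SD √(2 × 9) = 4.2% in the first-visit session and 6% in a later one.

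**The case against.** The strongest reply is that the plan already tests conditions against one another. On the natural reading CON is a level of exercise type, and Step 4 shows that the interaction withstands common drift. This stands: it would be wrong to say that the rest session goes unused. But a significant interaction is not required before the follow-up. When it is significant, it does not say whether AER, RE or both differ from rest, or in which direction.

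A reader might infer that drift will be reported as an exercise effect. The document does not say so. It nowhere states that a baseline-versus-post result alone will be credited to exercise, nor that these tests are run within each condition. An analyst would often see the same rise in CON: among simulated step-drift trials with a false AER or RE rise, CON also rose in about 70-82% at 1% drift, 90-95% at 2% and 99-100% at 3%. That is a useful warning sign, but significance in one condition and not in another is not a test of their difference.

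A reader might also infer that the primary result is compromised, since the abstract words the outcome loosely ("Our primary outcome for this study is the effect of acute exercise on ucOC in older adults with low muscle function", going on to name the high-function group). The Objectives, Primary Outcomes and statistical sections make it a low-versus-high comparison, in which drift common to both groups cancels.

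Finally, a condensed article may leave a full list of contrasts to an analysis plan. That is fair, and silence alone would be no finding. Here, however, the article does name its planned comparisons, and they do not address the exercise hypothesis.

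**Conclusion.** The point holds for the hypothesis that AER and RE each raise ucOC, and for that only. The named follow-up mixes any exercise effect with change over the session and between visits, and a time main effect is enough to open it. It would be too simple to describe its null as no change over the morning: for about two-thirds of the participants in each condition, the comparison is between days.

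The size is conditional. The documents give neither the amount nor the direction of drift, and the rates depend on its shape, above all for a single time point. With no drift, the gated follow-up declares a false rise in only about 4% of trials. With a 2% drift it does so in roughly 80-94%, against 2-3% for the contrasts with rest. These figures show how sensitive the rule is; they do not predict this trial's result. The change should be made, but the primary group comparison does not depend on it.

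**What to change.** Base any claim that an exercise type raises ucOC on two planned within-person contrasts, AER minus CON and RE minus CON. Use one prespecified summary per session: either the mean of the four post samples or the peak change that the protocol defines as its endpoint. Test each at 2.5%, or use Holm. The shared baseline cancels in the difference (in percentage change it remains only as a common divisor), and drift common to the sessions cancels with it.

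If contrasts at separate time points are wanted, two exercises by four times make eight. Adjust for all eight or label them descriptive. Keep the baseline-versus-post changes as description, and state that CON is a level of the exercise type factor.

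The cost is a change of wording in the analysis section, with no added samples or visits. The small downside is precision: the between-session contrast may be slightly noisier than the baseline-versus-post difference for the first-visit session (4.7% against 4.2% in Step 5).

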**Objective:**

The proposed trial will determine if circulating ucOC levels in older adults at baseline and following acute exercise are associated with parameters of muscle function and if the ucOC response to exercise varies between older adults with low muscle quality and those with normal or high muscle quality.

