## Introduction

### Background

Adults reach their peak muscle and bone mass in the third decade of life, after which an age-related loss of skeletal muscle and bone mass occurs [1,2]. Under certain conditions, for reasons that are not fully understood, this loss of bone mass (osteoporosis) and muscle (sarcopenia) is accelerated and, in some cases, occurs concurrently [3-5]. Emerging evidence suggests that this parallel and exponential loss of bone and muscle mass and strength is driven, at least in part, by bone and muscle crosstalk. The skeleton and skeletal muscle are closely linked anatomically, biochemically, and metabolically and modulate each other in endocrine and paracrine manners [6]. Many factors may be involved in this crosstalk, including genetics, changes in vitamin D and parathyroid hormone (PTH) levels, aging, increased levels of systemic and local inflammatory markers (ie, interleukin-6 [IL-6] and tumor necrosis factor), obesity and adipokines, mechanical loading, and altered hormones (ie, osteocalcin, resistin, and myostatin) [7,8]*.* The exact mechanisms involved in this crosstalk remain partially explored, although it has been proposed that undercarboxylated osteocalcin (ucOC) and possibly circulating osteoprogenitor (COP) cells may be mediators [6,9-12].

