#### Bone and Muscle Health

##### Dual Energy X-Ray Absorptiometry

Body composition and bone mineral density (BMD) will be assessed using a dual energy x-ray absorptiometry (DXA) scanner (Hologic, Horizon A, software version 5.6.0.4). Total BMD as well as the neck of the femur and lumbar spine BMD will be assessed. Lean body mass and fat mass will also be assessed. The DXA scan will ideally be performed in the morning following an overnight fast by experienced personnel. This will be completed by the AIMSS.

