##### Lower Limb Maximal Strength and LMQ

Participants will perform a one-repetition maximum (1RM) test on a leg press. This will be performed twice, with the first visit serving as familiarization. 1RM is defined as the heaviest weight lifted once with the proper technique and without compensatory movements [56]. Results from this study will guide appropriate prescription for the acute RE session.

LMQ, an estimate of specific force, has been shown to decrease with age and is described as the amount of force a muscle group can produce per unit of muscle mass [57]. We will calculate LMQ as follows:

LMQ = leg strength (kg)/(left leg lean mass [kg] + right leg lean mass [kg]) **(1)** [58].

Leg strength will be defined as the participants’ 1RM, and leg lean mass will be obtained from the DXA assessment.

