The proposed project aims to overcome this gap by characterizing ucOC levels in older adults with a spectrum of muscle functions and in response to an acute exercise intervention. Importantly, we will investigate this bone and muscle crosstalk by determining the associations between the parameters of muscle function (ie, muscle signaling, muscle mass, and muscle strength) and ucOC. In the future, we plan to directly assess this association at a cellular level in human primary myotubes (those prepared in this study) to determine the direct effects of ucOC on muscle protein signaling and glucose uptake. The results of this study will provide a greater understanding of skeletal muscle metabolism and the crosstalk between muscle and bone in the older adult population. We aim to establish ucOC as a biomarker for muscle function and bone and muscle crosstalk in older adults to target potential mechanisms for future therapeutic studies. We also aim to advance the development of personalized clinical exercise guidelines for sarcopenia and other musculoskeletal conditions.

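### BMI adjustment in the ucOC regressions: where the exposure is muscle mass, BMI contains it, so any fat effect on ucOC partly appears as a muscle association of opposite sign

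*Protocol article*

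**What the plan says.** The section Statistical Analysis and Determination of Sample Size gives one rule for all association models: they are multivariable regressions "adjusting for BMI and sex". It does not say which measurements are selected or which is the outcome.

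The targets have to be read from elsewhere in the article. The Objective in the Abstract asks whether ucOC levels, at baseline and after exercise, "are associated with parameters of muscle function". The Background gives strength and mass as examples of those parameters. The Discussion says the study will determine "associations between the parameters of muscle function (ie, muscle signaling, muscle mass, and muscle strength) and ucOC".

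The data for a different adjustment are already collected. For the DXA scan the article states: "Lean body mass and fat mass will also be assessed". The lean-mass exposure comes from the same scan: "leg lean mass will be obtained from the DXA assessment". The Background lists "obesity and adipokines" among many factors that may take part in bone–muscle crosstalk.

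**The concern.** BMI is presumably included to account for body size or adiposity. When the exposure is itself a muscle-mass measure, BMI cannot separate the two, because lean mass is a large part of BMI. Two people of equal BMI who differ in lean mass must differ in fat mass the other way. The muscle coefficient then mixes the muscle association with the reversed fat association.

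At stake is the reading of one of the links that the study sets out to describe. A negative fat–ucOC relation would create or inflate a positive muscle-mass association, which is the direction the hypotheses favour. A positive fat–ucOC relation would hide a real one.

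**Working it through.** **Reference figure.** The article gives no effect size or power for the regressions, so there is no stated figure to reproduce.

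**Inputs from the article.** Covariates BMI and sex; 54 participants, half women; lean and fat mass from DXA.

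**Inputs assumed (not in the article).** Within-sex SD of the fat index (fat mass/height²) 3.0 kg/m² and of the lean index 1.8 kg/m²; height SD 6.5 cm; fat–lean correlation 0.2 to 0.6; leg lean mass a near-constant share of lean mass. True muscle effect zero. The fat–ucOC correlation r is varied.

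**Algebra for height-indexed lean mass.** Write ucOC = bF × fat index + bL × lean index + error, with BMI ≈ fat index + lean index (the bone index is small and varies little). Substituting fat index = BMI − lean index gives

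ucOC = bF × BMI + (bL − bF) × lean index + error.

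The BMI-adjusted lean coefficient is therefore bL − bF. With bL = 0 and ucOC in SD units, bF = r/3.0 per kg/m². The spurious slope per SD of lean index is −(r/3.0) × 1.8 = −0.6r. At r = −0.3 this is +0.18.

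**Leg lean mass in kg.** This measure also varies with height, which at fixed BMI is not tied to fat, so the bias is diluted. The slopes and rejection rates below come from simulation. The ranges run over the fat–lean correlations.

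| Fat–ucOC correlation | Slope per SD, lean index (−0.6r) | Slope per SD, leg lean mass in kg | False positives at P<.05, leg lean mass in kg |
|---|---|---|---|
| −0.1 | +0.06 | +0.02 to +0.04 | about 5% |
| −0.3 | +0.18 | +0.07 to +0.11 | 7–11% |
| −0.4 | +0.24 | +0.09 to +0.15 | 9–15% |

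**Second set of assumptions.** Lean-index SD 1.7, fat-index SD 2.5, fat effect −0.4 SD per 2.5 kg/m², residual SD 1. The algebra gives 0.4 × 1.7/2.5 = +0.27 per SD of lean index, and the simulation agrees. With 49 participants and fat–lean correlation 0 to 0.5, false positives are 19–33% for indexed lean mass and 10–19% for total lean mass in kg.

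**Other exposures (second set, fat–lean correlation 0 to 0.7).** Leg-press 1RM takes a spurious slope of +0.03 to +0.08. LMQ takes none here, and −0.02 to −0.04 under a separate simulation, because dividing strength by leg lean mass removes most of the coupling.

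**Candidate repairs, leg lean mass in kg, r = −0.3.**
- Fat mass/height², or fat mass plus height, in place of BMI: slope about 0; false positives about 5%.
- Fat mass in kg without height: slope about +0.04 remains, because fat mass in kg still carries height.
- BMI dropped and nothing put in: the bias changes sign. For the lean index the slope is r × (fat–lean correlation), for example −0.3 × 0.4 = −0.12.

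**The case against.** Five points can be made for the plan as it stands.

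1. **The model is inferred.** The analysis section speaks only of selected measurements, and how lean mass is scaled may be settled in an analysis plan that is not shown. This stands as a limit. But the covariate set is stated, no other association model is given, and muscle mass is named as a target, so the inference is well supported.

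2. **No named outcome is touched.** A reader might infer that the primary comparison is contaminated. The article does not support that: the primary analysis is a repeated measures ANOVA with no BMI term, groups are formed on LMQ, and both secondary outcomes are protein comparisons. This objection stands in full.

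3. **The harm is conditional.** A reader might infer that the muscle association will come out with the wrong sign. That requires a sizeable fat–ucOC relation, for which the article gives no figure. Its Background lists obesity among possible crosstalk factors, not as a determinant of ucOC. At a correlation of −0.1 the error rate is close to nominal. This also stands. The article's own list only makes a fat effect plausible.

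4. **It is partly a choice of question.** Adjusting for BMI asks about muscle at a given body size, which is conventional, and no direct-effect estimand is stated. True, but the stated interest is the link between muscle and ucOC, and a coefficient equal to muscle minus fat answers that poorly.

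5. **Fat mass alone is not a clean substitute.** Correct; the height-indexed form, or height as an extra covariate, is needed.

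**Conclusion.** The point holds in a limited form. In association models with a muscle-mass exposure, adjusting for BMI moves part of any fat effect on ucOC into the muscle coefficient with the sign reversed. The shift equals the full fat effect per kg/m² for height-indexed lean mass and is smaller for leg lean mass in kg.

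For leg lean mass in kg with no true muscle effect, the size runs from negligible (about 5% false positives at a fat–ucOC correlation of −0.1) to moderate (9–15% at −0.4). These figures rest on assumed SDs, correlations and height spread. The direction rests only on the algebra and on a non-zero fat effect, with height unrelated to body composition given BMI and sex when lean mass is in kg. It does not matter which variable is the outcome, since the partial correlation is symmetric.

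This is an avoidable weakness in a supporting analysis, and not a flaw in the primary comparison.

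**What to change.** In regressions where the exposure is a muscle-mass measure, replace BMI by DXA fat mass/height squared, or by DXA fat mass and height as two covariates, and keep sex. Report the BMI-adjusted model beside it as a sensitivity analysis. Do not use fat mass in kg without height, and do not simply drop BMI. Models with LMQ as exposure can stay as they are.

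The cost is small. Fat mass is already measured at the screening DXA, and height is needed for BMI in any case, so no new data are required. Using fat mass and height separately costs one further degree of freedom. Comparison with earlier BMI-adjusted reports becomes less direct, which the sensitivity analysis covers.

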#### Participant Retention and Withdrawal

Once a participant is enrolled into the trial, the study coordinator will keep in contact with him or her for the entire study period. We estimate that the dropout rate in this population will be approximately 10%. Participants may withdraw from the study at any given time. The investigators or medical staff may also withdraw participants from the study due to safety or medical concerns.

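### The stated power of over 80% for a 4% group difference does not follow from the stated inputs: for one peak change per participant it is about 62% two-sided after 10% loss

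*Protocol article*

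**What the plan says.** All of the following is in the protocol article, section Statistical Analysis and Determination of Sample Size, unless noted.

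- **Endpoint.** "The primary endpoint for this study is the change in ucOC levels from baseline to the peak, postintervention sampling time point". The Primary Outcomes section likewise compares the peak change between the low and high muscle function groups, following the three interventions. For any one intervention this is one number per participant.
- **Sample.** 54 participants, "dichotomized as low muscle function versus high muscle function (27 per group").
- **Loss.** 10%, written as 5.4 of 54. Participant Retention and Withdrawal agrees: "We estimate that the dropout rate in this population will be approximately 10"%.
- **Effect and spread.** "this sample size will be large enough to detect an estimated 4% difference in changes in ucOC levels (SD 6%) between groups".
- **Error rates.** "type I error rate of 5%, type II error rate of 20%, and power of >80"%, computed in G*Power.
- **Analysis.** Repeated measures ANOVA over the sampling times, at the 5% level.

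The paragraph does not say which G*Power test was used, whether it was one- or two-sided, or what correlation or number of repeated measurements was assumed.

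**The concern.** Difference, SD, significance level, group size, loss and power are printed together, so they can be checked against each other. A difference of two-thirds of an SD with about two dozen participants per group is well short of what 80% power usually takes.

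This is the only sample-size justification for the primary group comparison. If the true power is lower than stated, a null result between the muscle function groups will be read as coming from a trial that had at most a 20% chance of missing the planned effect. With a two-sided test that chance is about 38% (100 − 61.8).

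**Working it through.** **Inputs from the document.** Difference 4 percentage points; SD of the change 6 percentage points; significance level 5%; 27 per group recruited; 10% loss.

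**Assumption.** Sidedness is not stated. Two-sided is taken as the default and one-sided is shown beside it.

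**Completers.** 54 − 5.4 = 48.6, so 48 (24 + 24) or 49 (25 + 24).

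**Standardised difference.** d = 4/6 = 0.667.

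**Method.** Two independent groups, one change score each. The test statistic follows a noncentral t distribution with n1 + n2 − 2 degrees of freedom and noncentrality d × √[n1·n2/(n1 + n2)]. For 24 + 24 this is 0.667 × √12 = 2.309 on 46 degrees of freedom, with two-sided critical value 2.013. For 27 + 27 it is 0.667 × √13.5 = 2.449 on 52 degrees of freedom, with critical value 2.007.

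**Attempt to reproduce the stated figure (over 80%).**

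| Completers | Two-sided 5% | One-sided 5% |
|---|---|---|
| 24 + 24 | 61.8% | 73.6% |
| 25 + 24 | 62.7% | 74.4% |
| 27 + 27 (no loss) | 67.2% | 78.0% |

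A normal approximation gives slightly higher values: 63.7% (24 per group) and 68.8% (27 per group) two-sided, 74.7% and 78.9% one-sided. The figure is not reproduced in any cell, even one-sided with no loss.

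**What 80% power would take.**

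- At 4% and SD 6%, two-sided: 36 per group gives 79.7% and 37 gives 80.8%, so 37 per group, 74 completers. One-sided: 29 per group, 58 completers.
- At 24 per group, two-sided: a difference of 4.96%, or an SD of about 4.84% if the difference stays at 4%.

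**Can the planned repeated measures ANOVA supply the missing power?** For the group effect averaged over m measurements with common correlation ρ, the noncentrality is f²·N·m/[1 + (m − 1)ρ], with f = d/2 = 0.333. With N = 48:

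- m = 1 returns 61.8%, as it should.
- m = 4: 86.2% at ρ = 0.4, 81.6% at 0.5, 72.8% at 0.7, 65.2% at 0.9.
- m = 5, ρ = 0.5: 83.1%.
- m = 12 (three conditions by four times), ρ = 0.6: 81.1%.

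Adjusting for baseline at 24 per group, with d divided by √(1 − ρ²), gives 74.2% at ρ = 0.5 and 80.7% at 0.6.

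Several routes therefore pass 80%. Each needs an m or a ρ that is not in the paragraph, and averaging over samples estimates something other than the peak change.

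**Group-by-time interaction.** With two times (baseline and peak), the interaction F is the square of the t statistic on change scores, so power is again 61.8%. A higher value appears only if a correlation is applied on top of an SD that is already the SD of the change.

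**The case against.** The strongest defence is that the paragraph names repeated measures ANOVA for the group comparison and names G*Power, which has repeated-measures routines. A calculation of that kind could have produced more than 80%, and a condensed article need not print every setting. This stands in part: the route by which the figure was obtained is unknown, and leaving out a correlation is not in itself a fault. It does not rescue the sentence, because the effect is expressed as a difference in change with the SD of that change, and the endpoint is one peak change.

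Sidedness is the second objection. The Hypotheses section is directional, expecting a larger rise in those with lower muscle function, so a one-sided test is conceivable. This limits the size of the shortfall: one-sided after loss, the chance of missing the planned effect is about 26% (100 − 73.6). It does not remove it.

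Three stronger readings are tempting and are not supported.

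- A reader might infer that the figure must come from averaging the four post-intervention samples at a correlation of 0.5. Other values of m and ρ also pass 80%, so the source cannot be identified.
- A reader might infer that 0.5 is a floor for the correlation, because the change scores share a baseline, and so that 81.6% is a ceiling. That holds only if baseline and post-intervention error variances are equal and the post-intervention errors independent. The article gives no variances, so no upper bound can be set this way.
- A reader might take 62% as unconditional. It rests on a two-sided test.

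**Conclusion.** The point holds. As written, the stated endpoint, difference, SD, group size and loss do not give more than 80% power. Two-sided, power is about 62% after loss and 67% without loss; one-sided, about 74% and 78%. No two-group version reaches 80%. The two-sided shortfall is large in participants: 74 completers needed against 48 or 49 expected.

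The conclusion rests on reading the primary endpoint as one peak change per participant for a given intervention, on 6% being the SD of that change, and on two independent groups of equal size. It does not rest on how rounding is done or on which of 48 or 49 completers is used. It is a finding about the stated figure. It does not show that the sample size must rise, or that the software calculation was wrong for whatever inputs were entered.

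**What to change.** Replace the power sentence, leaving the sample size at 54, with wording such as: *With 48 completers (24 per group), two-sided alpha 5% and SD 6%, power is about 62% for a 4% difference and 80% for a difference of about 5.0%.*

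If a repeated-measures or baseline-adjusted calculation was intended, state instead the test, its sidedness, the number of measurements and the assumed correlation, and bring the primary endpoint into line with the quantity that was powered.

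The cost is one corrected paragraph and a less favourable stated power. No participants are added and no procedure changes.
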